**Results:**

A total of 10,013 participants were randomized, and the recruitment process started on 9 March 2023. Secondary outcomes include (i) moderate COPD exacerbations; (ii) all-cause hospitalization; (iii) ICU admission; (iv) need for non-invasive ventilation; and (v) all-cause mortality, among others. All outcomes will be evaluated 12 months after recruitment.

**Clinical trial registration:**ClinicalTrials.gov, NCT05563675.

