### Objectives

The main objective of this intervention and research protocol is to determine whether evening administration of LAMA, as opposed to morning administration, is superior for the occurrence of hospitalization-requiring AECOPD or death from all causes. The intervention will have the following secondary objectives: (1) moderate COPD exacerbations, (2) all-cause hospitalization, (3) intensive care unit (ICU) admission, (4) need for non-invasive ventilation, (5) all-cause mortality, (6) Short-Acting Beta-Agonist (SABA) use / pick up rate, and exploratory endpoints (1) change in COPD Assessment Test (CAT) score, (2) change in Medical Research Council (MRC) score, and (3) change in the “soundly sleeping” parameter of CAT.

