### Trial design

The study is a pragmatic, registry-based, open-label, randomized controlled trial combining the utilization of the Danish nationwide health registries and the official Danish electronic letter system (Digital Post/e-Boks) into an innovative, decentralized trial requiring no study visits from participants. The trial will include patients receiving LAMA treatment that will be randomized 1:1 to either LAMA administration in the evening or the morning for 12 months.

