### Outcomes

The primary efficacy endpoint is the occurrence of hospitalization requiring AECOPD or death from all causes within 12 months. Secondary efficacy endpoints included (i) moderate COPD exacerbations; (ii) all-cause hospitalization; (iii) ICU admission; (iv) need for non-invasive ventilation; (v) all-cause mortality; (vi) SABA use/pick-up rate; and exploratory endpoints (i) relation between adherence and AECOPD hospitalization, (ii) change in CAT score, (iii) change in MRC score, and (iv) change in “soundly sleeping” parameter of CAT.

The details on the primary and secondary outcomes of the study can be seen in Tables 1, 2, and exploratory outcomes in Table 3.

**Table 2 tab2:** Secondary and exploratory endpoint definition.

Endpoint	ICD-10/ATC codes	Inpatient/outpatient/minimum required length of stay/other criteria
Moderate COPD exacerbations	Prednisolone: H02AB06 or Antibiotics: J01CA04, J01AA02, J01CR02, J01MA14	Excluding hospitalizations and emergency room visits: DJ441 (A)
Hospitalization (all-cause)		Inpatient, length of stay ≥24 h
Hospitalization in ICU (all-cause)		Inpatient, ICU, length of stay ≥24 h
Need for NIV	BGDA1	A or B
Mortality (all-cause)		Participant registered as dead in the CPR register.
SABA use/pick-up rate	R03AC02, R03CC02, R03AC03	Danish National Prescription Registry
Change in CAT score	Questionnaire	At 6 and 12 months
Change in MRC score	Questionnaire	At 6 and 12 months

The time frame is ≥1 day after randomization until the end of the study (12 months from randomization) for all outcomes. A = primary discharge diagnosis and B = secondary discharge diagnosis. COPD, chronic obstructive pulmonary disease; ICU, intensive care unit; NIV, non-invasive ventilation; CPR, Central (National) Person Registry; SABA, short-acting beta-2 agonists; CAT, COPD assessment test.

**Table 3 tab3:** Exploratory endpoint definition.

Endpoint	Data source or ICD-10 codes	Inpatient/outpatient/minimum required length of stay/other criteria
Relation between adherence and hospitalization-requiring AECOPD	Questionnaire, DJ440, DJ441	For hospitalizations: Type A diagnosis (primary discharge diagnosis). Inpatient and length of stay ≥24 h, or emergency room visits. Deaths excluded.
Change in CAT score	Questionnaire	At 6 and 12 months
Change in MRC score	Questionnaire	At 6 and 12 months
Change in CAT “soundly sleeping” parameter	Questionnaire	At 6 and 12 months

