## Data collection and management

### Plans for the assessment and collection of outcomes

In addition to what is obtained through the initial questionnaire, all information on baseline characteristics will be collected from Danish nationwide registries. This will be supplemented with data from the initial questionnaire on body mass index, smoking status (including pack-years), FEV1, and asthma. Information on adherence and symptom scores for exploratory outcomes will be obtained through questionnaires. The data from nationwide registries include age, gender, exacerbation history, comorbidities, and relevant medication details. All data used to assess clinical endpoints during the study will be collected from Danish nationwide registries.

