## Statistical methods

### Statistical methods for primary and secondary outcomes

The primary and all secondary outcomes will be analyzed using the intention-to-treat (ITT) approach, which encompasses the entire cohort of randomized participants in the study. Additionally, per-protocol analyses will be conducted for patients taking inhalation medication 6–7 days per week at the allocated administration time for the full duration of the study, along with modified ITT (mITT) analyses for those who have taken less than 6 days or more than 2 days per week for any amount of time. These analyses will be performed on both the primary and all secondary outcomes, providing a comprehensive evaluation of the study’s results.

The primary outcome (hospitalization-requiring AECOPD or death from all causes within 12) will be presented as a fraction with percentage and relative risk with a 95% confidence interval. The groups will be compared using a two-sided binomial test. The same principles will be applied to secondary binomial outcomes. For the SABA pick-up rate, the incidence rate and ratios will be calculated and presented (including 95% confidence intervals) and compared using the chi-squared test. Changes in CAT and MRC (respectively) will be reported as median differences with IQR and compared within and between groups with a paired two-sided Wilcoxon signed-rank test and an unpaired two-sided Wilcoxon rank-sum test. A subgroup analysis will be performed on the primary outcome with the following subgroups: adherence group (high adherence: ≥4–5 days per week of adherence), age (≥65 years), asthma overlap, coexisting heart failure, body mass index (>30 kg/), frequent exacerbator (>1 severe exacerbation within 12 months prior to baseline), and treatment with systemic beta-2 antagonist at baseline. A *p*-value of <0.05 will be considered significant.

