### Methods in analysis to handle protocol non-adherence and any statistical methods to handle missing data

Secondary analyses will include mITT and per-protocol analyses to provide a comprehensive evaluation of the study outcomes. No data on the primary outcome will be missing as national registries will be used for outcome assessment. Only self-reported outcomes such as MRC and CAT can be expected to be missing. It will be assumed all missing data will be missing at random or completely at random to allow for multiple imputations. No imputed data will be presented in the baseline table.

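### CAT and MRC are compared between arms on unadjusted change scores; adjusting for the Day-1 score would be modestly more precise at little cost

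*Protocol article*

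**What the plan says.** All references are to the protocol article.

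- **Analysis.** Statistical methods for primary and secondary outcomes states: "Changes in CAT and MRC (respectively) will be reported as median differences with IQR". These changes are then "compared within and between groups with a paired two-sided Wilcoxon signed-rank test and an unpaired two-sided Wilcoxon rank-sum test". The rank-sum part is the randomised comparison, and it takes no covariate. No baseline-adjusted model for these scores appears elsewhere in the article.
- **Status of the endpoints.** Objectives lists "change in COPD Assessment Test (CAT) score" and the corresponding MRC change as exploratory, and Outcomes does the same. Both also appear in Table 2, whose title covers secondary as well as exploratory endpoints.
- **Sleep item.** Outcomes adds "change in “soundly sleeping” parameter of CAT" as an exploratory endpoint. The analysis sentence names only CAT and MRC, so the sleep item has no stated test of its own.
- **Data source.** Plans for the assessment and collection of outcomes says: "Information on adherence and symptom scores for exploratory outcomes will be obtained through questionnaires". Table 4 marks a questionnaire on Day 1, at month 6 and at month 12. That CAT and MRC are scored on Day 1 is implied by the word change and by the paired within-arm test, but is not stated outright.
- **Missing data.** The section on non-adherence and missing data says: "Only self-reported outcomes such as MRC and CAT can be expected to be missing". It gives no expected response rate.

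**The concern.** Subtracting the baseline gives it a coefficient of exactly one. Unless the baseline and follow-up scores are perfectly correlated, that over-corrects: people who score high on Day 1 tend to come down and people who score low tend to go up, whatever their arm. This movement falls on both arms alike, so it does not bias the comparison, but it adds noise. A model that estimates the baseline coefficient from the data removes more of that noise and needs no further data.

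MRC raises a second, smaller issue. It is a short ordinal scale, and ranking differences between grades treats a one-step move at one end as equal to a one-step move at the other. A proportional-odds model does not subtract grades.

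What is at stake is precision on the patient-reported symptom outcomes of a trial whose rationale concerns night and early-morning symptoms. The primary outcome and its sample size are not involved.

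**Working it through.** **Plan's own figure.** The article gives no power, SD or correlation for CAT, MRC or the sleep item, so there is nothing to reproduce for these endpoints. Its one design figure, 6,662 (3,331 per arm) for the primary outcome, is reproduced with a continuity-corrected two-proportion formula using p1 = 16,000/178,000 and a relative reduction of 0.25 × 0.844 = 21.1%. It does not depend on how the symptom scores are analysed.

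**Inputs.**
- Randomised: "A total of 10,013 participants were randomized" (abstract, Results). Allocation is 1:1 (Trial design), so about 5,006 per arm.
- Alpha 0.05 two-sided and power 0.80, borrowed from Sample size.
- r, the correlation between the Day-1 and follow-up score. This is an assumption, taken from 0.5 to 0.8.

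**Variance of the arm difference**, with n per arm and the same SD σ at both times:
- mean change: (2/n) × 2σ²(1 − r)
- ANCOVA on the follow-up score: (2/n) × σ²(1 − r²)
- ratio: 2(1 − r)/[(1 − r)(1 + r)] = 2/(1 + r), which exceeds 1 for every r below 1.

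**Detectable difference in SD units** = (1.960 + 0.842) × √(2/5,006) × √k = 0.0560 × √k, with k = 2(1 − r) for change and k = 1 − r² for ANCOVA. At r = 0.5 this gives 0.0560 × √1 = 0.0560 and 0.0560 × √0.75 = 0.0485. The last column is 10,013 × (1 + r)/2.

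| r (assumed) | variance ratio 2/(1+r) | detectable, change | detectable, ANCOVA | 10,013 on change is worth, with adjustment |
|---|---|---|---|---|
| 0.5 | 1.33 | 0.0560 | 0.0485 | 7,510 |
| 0.6 | 1.25 | 0.0501 | 0.0448 | 8,010 |
| 0.7 | 1.18 | 0.0434 | 0.0400 | 8,511 |
| 0.8 | 1.11 | 0.0354 | 0.0336 | 9,012 |

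**With non-response.** If 60% answered (an assumption; 3,003 per arm), the pairs become 0.0723 against 0.0626 at r = 0.5, and 0.0457 against 0.0434 at r = 0.8.

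**Check on the planned test itself.** The ratio above is for mean change against linear ANCOVA, not for a Wilcoxon test. Rank-sum on change was therefore simulated directly, with 1,000 per arm, 1,500 replicates, assumed score distributions, and an effect sized for 80% ANCOVA power on the underlying continuous scale.

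| Score | r | rank-sum on change | ANCOVA | rank-ANCOVA |
|---|---|---|---|---|
| CAT-like (0–40) | 0.5 | 66% | 80% | 77% |
| CAT-like | 0.65 | 69% | 79% | 76% |
| CAT-like | 0.8 | 74% | 81% | 76% |
| MRC-like (5 levels) | 0.5 | 56% | 73% | 72% |
| MRC-like | 0.65 | 61% | 74% | 72% |
| MRC-like | 0.8 | 56% | 63% | 61% |

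A six-level item resembling the sleep item gave 55% against 70%, 59% against 70% and 58% against 66% (rank-sum on change against ANCOVA). With no effect, CAT-like rejection rates were 4% to 5% for all methods. The simulation confirms the direction for the planned test. Its power gaps are not those of this trial, which has about five times as many participants per arm.

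**The case against.** The strongest reply is that the plan contains no error here. A rank-sum test on change is valid under randomisation, it is a conventional choice for bounded questionnaire scores, and at this sample size either analysis detects effects below a tenth of an SD. All of that stands, and it settles the priority. It does not remove the point, because the same data would give a more precise comparison.

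Four stronger readings are tempting, and the document does not support them:

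- **That the comparison is biased.** A reader might infer this from regression to the mean or from floor effects. Both act equally on the randomised arms, and the simulated type I error is nominal.
- **That the plan fixes this test for the sleep item.** The analysis sentence names CAT and MRC only. Coverage of the item as a component of CAT would be an inference.
- **That the trial forgoes exactly 11% to 33% more responders.** That range comes from the linear formula with an assumed r. It is not the relative efficiency of the Wilcoxon test.
- **That adjustment cures the scale problems.** Linear ANCOVA on CAT still counts equal point moves as equal and does not remove a floor. Proportional odds brings an assumption that the rank-sum test does not need.

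It may also be said that Day-1 CAT and MRC scores are not explicitly listed among the baseline items. That is so, but the planned change scores and the paired within-arm test cannot be computed without them, so the remedy asks for nothing beyond what the plan already needs.

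**Conclusion.** The point holds as a low-priority gain in efficiency for CAT and MRC. The planned between-arm test is valid but discards some precision. In the linear approximation the variance is inflated by a factor of 1.33 at r = 0.5, falling to 1.11 at r = 0.8. In detectable difference the saving from adjustment is 0.0560 − 0.0485 = 0.0075 SD at r = 0.5 and 0.0354 − 0.0336 = 0.0018 SD at r = 0.8, before non-response.

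These figures rest on equal variances at baseline and follow-up, on an r that the document does not give, and on Day-1 scores being held. The endpoints are mainly exploratory. A reader might conclude that a worthwhile symptom effect is likely to be missed; with detectable differences already near 0.04 to 0.06 SD at full response, the figures do not show that.

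**What to change.** Before outcome data are seen by arm, amend the between-arm analysis as follows:

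- **CAT total:** a linear model of the 6-month and 12-month score on arm, with Day-1 CAT as covariate. Report the adjusted mean difference with 95% CI.
- **MRC:** a proportional-odds model adjusted for Day-1 MRC, reporting the odds ratio with 95% CI, or a rank-ANCOVA if the proportional-odds assumption is not wanted.
- **CAT sleep item:** state its analysis explicitly, using the same approach as for MRC.
- **Rank-sum test on change:** keep it as a sensitivity analysis, so that the published method is still reported.

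The cost is a short documented amendment, made after randomisation and therefore needing a stated reason and date, plus the proportional-odds assumption where that model is used. No further data collection is needed beyond the Day-1 score that the change endpoint already requires.

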### Interim analyses and stopping guidance

A Data and Safety Monitoring Board (DSMB) will be appointed and act according to a charter agreed by the investigators and approved by the sponsor. Six months after the recruitment of the last patient, an interim analysis, based on the ITT population, will be performed to evaluate the continuation of the trial. As main statistical measures, an O’Brien-Fleming plot of the primary endpoint and mortality (calculating *Z*-scores) will be performed. The interim analysis will be performed and presented by a sub-investigator not otherwise involved in the data collection or analyses, overlooked by the trial statistician. The data will be presented in a blinded fashion.

At the interim analysis, the event rate and effect size for the primary endpoint, as well as the safety and progress of the study, will be assessed by the DSMB, and follow-up duration may be adjusted accordingly. Safety will be assessed by comparing event rates to the event rate presumption used for the initial sample size determination. The study may stop for futility if it is deemed improbable to achieve a follow-up duration sufficient to detect a clinically important effect size. The study will not stop for superior efficacy at interim analysis. We wish to prioritize increasing the likelihood of having sufficient power to conclude on the secondary endpoints at the final analysis.

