### Methods for additional analyses (e.g., subgroup analyses)

Continuous baseline variables will be summarized using means, 95% confidence intervals, medians, and interquartile ranges according to distribution. Categorical variables will be compared using frequencies and proportions. All statistical tests will be two-sided, and *p*-values of <0.05 will be considered statistically significant.

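### A blanket p<0.05 rule covers six secondary outcomes, repeat analysis sets and seven subgroup factors, while the trial means to conclude on the secondary endpoints without error control

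*Protocol article*

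**What the plan says.** All references are to the protocol article.

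- **Outcomes.** There is one primary endpoint. The section then lists six secondary ones: "Secondary efficacy endpoints included (i) moderate COPD exacerbations; (ii) all-cause hospitalization; (iii) ICU admission; (iv) need for non-invasive ventilation; (v) all-cause mortality; (vi) SABA use/pick-up".
- **Statistical methods for primary and secondary outcomes.** The primary and secondary outcomes are analysed by ITT. Per-protocol and mITT analyses are added, and "These analyses will be performed on both the primary and all secondary outcomes". On subgroups: "A subgroup analysis will be performed on the primary outcome with the following subgroups", followed by seven factors (adherence, age, asthma overlap, heart failure, body mass index, frequent exacerbator, systemic beta-2 antagonist). The section ends with "A *p*-value of <0.05 will be considered significant".
- **Methods for additional analyses (e.g., subgroup analyses).** The threshold is repeated without exception: "All statistical tests will be two-sided, and *p*-values of <0.05 will be considered statistically significant".
- **Interim analyses and stopping guidance.** The trial will not stop for efficacy. The reason given is "We wish to prioritize increasing the likelihood of having sufficient power to conclude on the secondary endpoints at the final analysis".
- **Section on non-adherence and missing data.** The extra populations get a lower label: "Secondary analyses will include mITT and per-protocol analyses to provide a comprehensive evaluation of the study outcomes".

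The article gives no testing order, gate, adjustment or descriptive label for the secondary endpoints or subgroups.

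**The concern.** Many trials report unadjusted secondary p-values and treat them as supportive. This article goes further in two ways. It gives every test the same threshold for significance, and it gives the wish to conclude on the secondary endpoints as its reason for not stopping early for efficacy. Read together, these let any of the six secondary endpoints be declared significant on its own p-value. Nothing in the text makes that depend on the primary result.

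At stake is a claim about mortality, intensive care admission or non-invasive ventilation that rests on one nominal p just under 0.05 out of six. The same applies to a subgroup claim drawn from seven factors.

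**Working it through.** **1. The plan's own figure.** The article gives no family-wise error figure. It gives a sample size for one test at two-sided 0.05 with power 0.80 (*Sample size*), which can be reproduced:

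- Control risk: 16,000/178,000 = 8.99%.
- Diluted relative reduction: 0.25 × 0.844 = 21.1%, so the evening risk is 8.99% × 0.789 = 7.09%.
- The usual two-proportion formula gives 3,226 per arm. With the continuity correction it gives 3,331 per arm, or 6,662 in total, as printed.

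The design alpha therefore belongs to the ITT primary alone. The analyses below do not inflate it.

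**2. Six secondary outcomes, ITT only.** With no true effect and k independent tests at 0.05, the chance of at least one p<0.05 is 1 − 0.95^k.

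- k = 6: 1 − 0.95^6 = 26.5%. Expected false positives: 6 × 0.05 = 0.30.

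The outcomes overlap clinically, so independence is an upper reference. Simulating six normal test statistics with a common correlation, at a cut-off of 1.96, gives:

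| Assumed correlation | At least one false positive |
|---|---|
| 0 | 26.6% (exact 26.5%) |
| 0.3 | 24.0% |
| 0.5 | 20.7% |
| 0.7 | 16.5% |
| 0.9 | 10.9% |

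The correlations are assumptions; the article gives none. Even at 0.9 the risk is about twice 5%.

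**3. Subgroups, primary outcome only.** Seven interaction tests: 1 − 0.95^7 = 30.2% if independent. The article does not say whether interaction or within-level tests are meant.

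**4. Repeating the six secondaries in three populations.** Eighteen independent tests would give 1 − 0.95^18 = 60.3%. The populations share patients, so this is only a ceiling. Two simulations allow for the overlap:

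- Test statistics correlated 0.8–0.9 between populations, with outcomes either independent or moderately correlated: 33–46%.
- Patient-level data with 10,013 participants and assumed event rates, a 65% per-protocol share and mITT either nested or disjoint: 39–52%.

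None of these inputs except the 10,013 is in the article. The direction is firm (above the ITT-only figure), but the size is not.

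**5. Effect of control.** Bonferroni at 0.05/6 = 0.0083 gives 1 − (1 − 0.0083)^6 = 4.9% if independent. Holm, or a fixed order at 0.05, keeps the six at or below 5% whatever the correlation. The primary alpha and the 6,662 do not change.

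**The case against.** The strongest reply is that the article states a threshold and is silent on multiplicity. Testing order and adjustment commonly sit in the statistical analysis plan, which is not shown, and a journal article is condensed. That would answer a bare omission. Here, however, the text applies 0.05 to all tests, and any hierarchy in an unseen plan would have to qualify that published rule. It is fair to add that the article nowhere says adjustment will be withheld, or that a secondary claim may follow a null primary. It only fails to prevent it.

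A second reply is that a ranking already exists: one primary endpoint, secondary and exploratory tiers, ITT as the main approach, and the other populations called secondary analyses. This stands, and it protects the primary. It does not control error among the secondary endpoints.

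Several stronger readings are tempting and do not hold:

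- **That a false-positive claim is likely.** For the six ITT secondaries the risk is about one in six to one in four. Pooling the 18 population tests with seven subgroup tests gives 72% if independent and 53–68% in the simulations. That pool mixes tiers the article separates and rests on correlations it does not give.
- **That the repeat populations give 60%.** This treats overlapping sets of patients as independent.
- **That the subgroups give 51%.** This is 1 − 0.95^14, for 14 independent within-level tests that the article does not specify. Allowing for dependence, the patient-level simulation gave 35–37% for that design.
- **That the mITT, per-protocol and subgroup results are all meant to support claims.** The interim sentence speaks only of secondary endpoints.

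**Conclusion.** The point holds for the secondary endpoints and, to a lesser degree, for the subgroups. The article fixes one significance rule for all tests and states an intention to conclude on the secondary endpoints, with no error control for those conclusions.

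Under a global null, the six ITT secondaries carry a 26% risk of at least one false significant result if independent, and about 17–24% at assumed common correlations of 0.7 to 0.3. Seven subgroup interaction tests carry up to 30%. The mITT and per-protocol repeats raise the secondary risk by an amount that cannot be fixed from the article. The ITT primary is not inflated by any of this, so its conclusion is not in question on this ground. The change should be made before outcome data are analysed.

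**What to change.** Replace the two blanket threshold sentences with one paragraph that does the following:

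1. Confines the p<0.05 rule to the ITT analysis of the primary outcome.
2. For the six ITT secondary outcomes, chooses one of two courses. Either control the family-wise error (for example by Holm or a prespecified fixed order, tested only after a significant primary), or label them supportive and report 95% intervals without significance claims. Several conventions are acceptable; leaving the choice open is not.
3. Reports mITT, per-protocol and subgroup results as estimates with 95% intervals.
4. Judges baseline subgroups by treatment-by-subgroup interaction, not by p-values within levels. The adherence factor describes behaviour after randomization, so it is not a baseline subgroup and stays with the estimates under item 3.

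If the statistical analysis plan already contains such a scheme, the published wording should be brought into line with it.

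No new data are needed, and the relative risks, rate ratios and intervals already planned for the outcomes are kept. The downside is that some secondary results with p just under 0.05 can no longer be called significant. Under a gate, that would apply to all six if the primary is not significant.
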